### Outcome assessment timeline

Screening: The RA will invite potential participants, answer questions, and gather informed consent. The RA will complete a screening form checking eligibility criteria for all approached individuals. Panoramic radiographs will be requested, and recruitment will be conditional based on the results from the imaging (as in the exclusion criteria). As a piloting process, we collect data on gender conformity by two questionnaires, the Conformity to Feminine Norms Inventory-45 and Conformity to Masculine Norms Inventory-30 [52, 53].Baseline: Participants will return for baseline evaluation, *intraoral scanning*, and collection of sociodemographic information (including gender questionnaires) and medical and dental history (including patient experience with previous dentures). Participants will be asked to complete the MDSQ and OHIP-EDENT, and a dentist with experience in providing full dentures will apply the FAD instrument.Delivery and denture adjustments: Immediately after the end of the delivery appointments, the FAD instrument will be applied for each denture pair (same dentist as on baseline). The adverse effects form will be completed at the same time, as well as during each post-delivery appointment, scheduled or not.First follow-up (3 months): Participants will complete the outcome data questionnaires, the MDSQ and OHIP-EDENT. We will administer both questionnaires with a tablet computer away from the clinical setting. In turn, we will complete the FAD and adverse effects form, as described in the previous paragraph plus the colorimetric evaluation of denture bases.Second follow-up (6 months): Same as in previous time point (questionnaires and colorimetric analysis). At the end of the trial, participants will choose which overdenture they wish to keep. When faced with a choice, one is presented with the choices and the associated costs, which allows for a rationale decision. This is particularly important as dentures are typically not covered by the health care provider. Then, we will conduct individual semi-structured interviews about their experiences with the IMOs. The rich descriptive data obtained by qualitative interviews will help further explicate the quantitative findings. An experienced qualitative researcher will be responsible to conduct the interviews outside of the clinic using an interview guide with open-ended questions. Given the explanatory nature of this mixed-methods design, the interview guide will be created iteratively based on the quantitative outcomes which require further explanation. Each interview will be audio-recorded and transcribed verbatim.

At baseline, we will register time (professional and patient) and materials use for cost analyses. The same procedures will be repeated during every appointment in the trial, scheduled or not.6.Long-term follow-up: Once participants provide 6-month data and choose the denture pair they wish to keep, we will continue their follow-up. For those participants who have no preference for one specific pair, the last pair used will be kept. Then, we will schedule them for yearly appointments until 5 years, during which the same outcome data will be gathered. In the meantime, participants may contact the research team for unscheduled appointments. Any event such as maintenance and clinical complications, as well as time and procedures done, will be reported as part of collected outcome data.

### Sample size estimation

The planned enrollment comprises 26 participants, based on overall patient satisfaction. A minimal important difference of 10 mm (10% of the VAS) was used for the estimation, as done in previous RCTs [41, 54]. A standard deviation of 7.5 mm was chosen for the difference in satisfaction [55]. Considering a 2-sided alpha of 0.01 to compensate for the number of secondary outcomes and a power of 90%, the RCT requires *n* = 21 for superiority hypothesis testing (i.e., the confidence interval for between-treatment differences would exclude zero) [56]. The final sample size is drawn from including further 20% to the planned *n* to compensate for possible dropouts; although withdrawals will unlikely pass 10% [41, 55, 57], additional participants may be lost due to aging-related issues (e.g., worsening of systemic diseases, and death).

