**Methods/design:**

We will recruit 26 completely edentulous participants (any sex/gender) based on the following eligibility criteria: age ≥ 60 years, no tooth extraction in the past 12 months, two implants in the lower jaw, and need for new dentures in both jaws. Each participant will receive two denture pairs, either manufactured by 3D printing or traditionally, to be worn in a random order. A timeline of 3 months with each denture pair will be considered for outcome assessment (total: 6 months). Patient satisfaction with dentures will be measured by the McGill Denture Satisfaction Questionnaire. We will evaluate other patient-reported outcomes (including oral health-related quality of life) as well as clinician-assessed quality and cost. At the end of the trial, participants will choose which denture pair they wish to keep and interviewed about their experiences with the 3D-printed IMO. The quantitative and qualitative data will be incorporated through an explanatory mixed-methods strategy. A final quantitative assessment will happen after 12 months with the preferred IMO to assess the long-term performance and maintenance needs.

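### The printed sample-size inputs give about 12 participants, not 21, so the stated difference, SD, power and n cannot all be right

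*Protocol article*

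**What the plan says.** The trial is a two-period cross-over: "Each participant will receive two denture pairs, either manufactured by 3D printing or traditionally, to be worn in a random order". The Sample size estimation section of the Protocol article then gives every input that a paired calculation needs:

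- Difference: "A minimal important difference of 10 mm (10% of the VAS) was used for the estimation".
- SD: "A standard deviation of 7.5 mm was chosen for the difference in satisfaction".
- Error rate: "Considering a 2-sided alpha of 0.01 to compensate for the number of secondary outcomes", with power set at 90%.
- Result: "the RCT requires *n* = 21 for superiority hypothesis testing".

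The figure of 21 precedes the dropout allowance. A further 20% is added afterwards to reach 26 (21 × 1.2 = 25.2, rounded up). The section gives no per-period SD, within-person correlation or formula.

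**The concern.** Because each participant serves as their own control, the SD of the difference is the correct input for a paired calculation, and no correlation is needed once it is given. A standardised difference of 10 / 7.5 = 1.33 is large, and 21 participants is far more than it requires at 90% power, even at alpha 0.01.

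At stake is the only justification given for the size of the primary comparison. A reader cannot tell whether the trial was planned around an SD of the difference of 7.5 mm or around a larger value, and expected precision depends on which it was. A later trial that reused 7.5 mm as the SD of a paired difference could plan about 12 participants; if the true value were 10.6 mm, 12 would give only about 58% power.

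**Working it through.** **Inputs** (all from Sample size estimation): difference d = 10 mm; SD of the difference s = 7.5 mm; two-sided alpha 0.01; power 0.90; stated n = 21.

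**1. Attempt to reproduce 21 from the inputs as printed.**

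- Normal approximation: n = [s(z₀.₉₉₅ + z₀.₉₀)/d]² = [7.5 × (2.576 + 1.282)/10]² = 8.4, so 9.
- Paired t-test (noncentral t, n − 1 df, noncentrality d√n/s): n = 12, with power 90.7%.
- Cross-over t-test (n − 2 df, allowing for a period or sequence term): power is 89.4% at n = 12 and 93.0% at n = 13, so n = 13.
- One-sided alpha 0.01, paired t: n = 11.

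None of these is near 21. The dropout allowance does not explain the gap, since 21 is the figure before inflation.

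**2. What the printed inputs imply at n = 21.**

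- The noncentrality is 10 × √21 / 7.5 = 6.11 against a critical t of 2.845 (20 df). Power is 99.9% with either n − 1 or n − 2 df.
- The difference detectable with 90% power is about 6.9 mm.

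**3. Which changes to a single input would give 21.**

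| Change, other inputs held | Paired t result |
|---|---|
| SD of the difference = 7.5 × √2 = 10.6 mm | n = 21; power 91.6% (n − 1 df) or 91.3% (n − 2 df); n = 20 gives 89.7% or 89.3% |
| SD of the difference anywhere from about 10.56 to 10.87 mm (n − 1 df) | n = 21 |
| Difference = 7 mm, SD of the difference 7.5 mm | n = 21; power about 91% (n = 20 gives 89.0%) |

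**4. Where the √2 could come from.** The factor √2 is right if 7.5 mm is the within-participant (residual) SD. If 7.5 mm is an ordinary per-period SD across participants, the SD of the difference is 7.5 × √[2(1 − ρ)], where ρ is the within-person correlation:

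| ρ | SD of the difference (mm) | n (paired t) |
|---|---|---|
| 0 | 10.6 | 21 |
| 0.25 | 9.2 | 16 |
| 0.5 | 7.5 | 12 |

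A per-period SD of 7.5 mm therefore gives 21 only with zero correlation.

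**5. Effect on expected precision at n = 21** (half-width = t × s/√21):

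| SD of the difference | 99% interval (t = 2.845) | 95% interval (t = 2.086) |
|---|---|---|
| 7.5 mm | 4.7 mm | 3.4 mm |
| 10.6 mm | 6.6 mm | 4.8 mm |

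The 99% interval matches the alpha used for sizing; the 95% interval is the one named in the Quantitative analysis section.

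**The case against.** The strongest defence is that the discrepancy is on the safe side. With 21 evaluable participants power is 99.9% if the SD of the difference is 7.5 mm and about 91–92% if it is 10.6 mm. Both exceed the stated 90%, and enrolment would not change. This stands, and it limits the severity.

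Three stronger readings are tempting, and the document does not support them.

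- *A reader might infer that 7.5 mm must be a mislabelled per-period SD.* That rests on a numerical match alone. The sources cited for the SD and for the method are not at hand. Other single changes also give 21, such as a 7 mm target, although the section does fix 10 mm as a tenth of the scale.
- *A reader might simply relabel 7.5 mm as per-period and multiply by √2.* This is valid for a residual SD, but for a per-period SD only at zero correlation. At ρ = 0.5 it would put a new error into the text.
- *A reader might argue that the error undermines a margin.* The article sizes the trial "for superiority hypothesis testing (i.e., the confidence interval for between-treatment differences would exclude zero") and sets no non-inferiority or equivalence margin.

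The defence does not touch the mismatch itself. All the inputs and the answer are printed, and nothing elsewhere in the article reconciles them. Nor could a fuller protocol make the printed difference, SD, alpha, power and n agree.

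**Conclusion.** The point holds as an error in the stated sample-size justification. The printed inputs require 12 participants (13 with n − 2 df), where the article states 21. At 21 the power is about 99.9%, not 90%. The conclusion assumes a paired or two-sequence cross-over t-test on the within-person difference, which is what the stated SD and design imply; choice of approximation or rounding does not close the gap.

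An SD of the difference of 10.6 mm would reproduce 21 with about 91–92% power. It is a plausible explanation but an unverified one. Neither reading of the SD shows underpowering. The severity is moderate: the text needs correcting, but the size of the trial does not.

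**What to change.** Check the source of the 7.5 mm, then restate the sentence so that difference, SD, power and n agree.

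- If 7.5 mm is the SD of the within-person difference, give the power at n = 21 as about 99.9% for 10 mm (equivalently, 90% for about 6.9 mm).
- If it is a within-participant (residual) or a per-period SD, say which. Give the assumed within-person correlation where it applies, the resulting SD of the difference, and the matching power (about 91–92% at n = 21 if that SD is 10.6 mm).
- If another input, such as the target difference, was different in the actual calculation, correct that input instead.

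Naming the test or formula used would let a reader reproduce the figure. The cost is a source check and one corrected sentence. Enrolment of 26 need not change.

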### Outcome measures

The primary outcome of this trial will be the general satisfaction of participants with their full dentures, in line with its ultimate goal. In addition, secondary measures will include satisfaction-specific aspects (e.g., chewing ability and esthetics), oral health related quality of life (OHQoL), clinical quality of the dentures, and treatment costs, all based on a public health system perspective.The McGill Denture Satisfaction Questionnaire (MDSQ) [37, 38] will be used to measure overall satisfaction, and satisfaction with specific aspects of the denture—ability to chew, comfort, stability, esthetics (appearance), ability to speak, and ability to clean. Participants will rate their satisfaction on a 100-mm visual analogue scales (VAS) with anchors representing “no satisfaction at all” to “complete satisfaction.” Participants will receive training with VAS before answering the MDSQ. Previous studies have shown good properties for the MDSQ. Besides good internal consistency and reproducibility [38, 39], its ability to discriminate between different clinical conditions denotes good construct validity [38, 40, 41]. At the last follow-up, participants will be asked about which denture pair they prefer, if any, and their reasons.OHQoL: This construct, conceptualized as the “subjective evaluation of the individual’s oral health, functional well-being, emotional well-being, expectations and satisfaction with care, and sense of self” [42], will be assessed by the Oral Health Impact Profile for Edentulous Patients (OHIP-EDENT) questionnaire. OHIP-EDENT is a short version (20 questions) of the original 49-question OHIP (Oral Health Impact Profile) tested specifically with edentulous individuals [43]. Questions can be grouped into subscales, corresponding to domains/dimensions of perceived impact, including functional limitation or social disability. This short version shows good reliability and discriminant validity, akin to the original OHIP [43]. Despite the seven original subscales, a four-domain model based on recent factor analysis studies will be used [44, 45].Clinical denture quality: This trial will use the Functional Assessment of Dentures (FAD) instrument to assess denture quality [46, 47]. FAD is composed of questions about relevant clinical parameters, including dental occlusion/articulation, denture retention, and stability. A single dentist will apply the instrument without removing the dentures from the mouth, which will ensure that s/he cannot see the staircase topography of CAD/CAM fabrication. The color of the denture base materials will be verified at baseline and after 3 months with a Vita EasyShade portable spectrophotometer [48]. Upper dentures will be placed on a black background and three measures will be taken from the center of the palatal vault, at the polished side. Color measures will be expressed according to the CIELCh and CIELab systems. Clinically evident damage (e.g., fractured base or teeth, stains) to denture constituents will be also reported.Cost: Data on both the direct and indirect costs of each fabrication method will be gathered, as done previously [16, 49]. The number of clinical visits for denture fabrication and adjustments will be reported separately, including non-scheduled visits. Total cost per fabrication method will be described in terms of expenses with human resources (time and CAD$) and materials (consumables/equipment use, CAD$). Yearly cost differences, or $(Δ), will be calculated based on the expected lifetime of 5 years for a pair of dentures, by dividing total cost differences by five. After the last follow-up, participants will answer four questions on their willingness-to-pay for each denture pair: (1) If you were to choose A over B, how much are you willing to pay for it? (2) Are you willing to pay the $(Δ) to have A over B? (3) Are you willing to pay the $(Δ) to have A over B by monthly installments (12 months)? (4) Do you think that a public health plan should cover the cost of these treatments? Both or only A or B.

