### Analytical plan

#### Quantitative analysis

We will enter and analyze outcome data in a blind fashion at the end of data collection. The TC will enter data in spreadsheets by randomly coding the interventions as 1 and 2, and the data analyst will be unaware of their meaning until the end of statistical testing. Data will undergo descriptive analysis, with substantial deviations from normality leading to variable transformation. Generalized estimating equations (GEE) will be used to test the effect of interventions, follow-up time, and gender as independent variables, with 95% confidence intervals. Other approaches to assess the primary outcome will involve the inclusion of age, baseline results, and previous denture wearing in separate models, one covariate at a time.

A limitation with regard to GEE is that compared to parametric normal theory methods that necessitate the missing data to be missing at random, GEE methods impose a more stringent condition, requiring the data to be missing completely at random. Our results will be evaluated according to the intention-to-treat principle. In the case of unbalanced missing data among interventions or loss of 5% (*n* > 2) or more of participants, different strategies will be attempted for imputing primary outcome data, as recommended by Dziura et al. [60]; multiple imputation will be used for patient satisfaction based on least squares regression with at least five datasets. In the case of “missing not at random” (MNAR) data, analyses will be repeated after a baseline-observation-carried-forward approach (i.e., withdrawn participants will be considered as dissatisfied as prior to receiving dentures). A second analysis will be performed with imputed values and cross-checked.

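### The alpha of 0.01 said to compensate for the number of secondary outcomes is not carried into the analysis, and even if applied it would not guarantee a 5% family-wise error across the secondary measures named

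*Protocol article*

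**What the plan says.** The Sample size estimation section of the protocol article gives the level and its purpose together: "Considering a 2-sided alpha of 0.01 to compensate for the number of secondary outcomes and a power of 90" per cent. It names no target for the family-wise error, no adjustment procedure and no count of tests.

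The Outcome measures section names one primary outcome, general satisfaction, and four secondary areas: specific aspects of satisfaction, oral health-related quality of life, clinical denture quality and cost. It then breaks two of these down. The satisfaction questionnaire (MDSQ) covers "ability to chew, comfort, stability, esthetics (appearance), ability to speak, and ability to clean", which is six aspects. For the OHIP-EDENT, "a four-domain model based on recent factor analysis studies will be used". Clinical quality is scored with the FAD. Colour, number of visits, willingness to pay, adverse effects and denture preference are also collected.

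The Quantitative analysis section says: "Generalized estimating equations (GEE) will be used to test the effect of interventions, follow-up time, and gender as independent variables". The same sentence sets 95% confidence intervals. The 0.01 level does not appear there.

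**The concern.** A protocol article may leave the handling of secondary outcomes to an analysis plan. This one makes a positive statement instead: the chosen alpha takes care of the number of secondary outcomes. That can be checked against two other parts of the same document, the list of measures and the analysis.

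The risk lies in the secondary results. Suppose the two fabrication methods do not differ. The more aspects and domains are compared without effective control, the more likely it is that one of them (esthetics, comfort or one OHIP-EDENT domain, say) looks different by chance. A reader who trusts the stated compensation would take that difference as protected. The interview guide is to be built from the quantitative outcomes that need explaining, so a chance finding could also steer the qualitative phase. The dissemination and discussion sections direct the results to clinicians, continuing education and public programmes.

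**Working it through.** **Inputs.** From the sample size section: two-sided alpha 0.01 and power 90%; "A minimal important difference of 10 mm (10% of the VAS) was used for the estimation"; "A standard deviation of 7.5 mm was chosen for the difference in satisfaction"; "the RCT requires *n* = 21 for superiority hypothesis testing"; "The final sample size is drawn from including further 20% to the planned *n* to compensate for possible dropouts". From the outcome section: 1 primary outcome; 6 MDSQ aspects + 4 OHIP-EDENT domains + 1 FAD = 11 secondary measures; 12 tests with the primary. From the analysis section: 95% intervals, so 0.05 per comparison. Assumed, because the document gives neither: a family-wise target of 0.05, and equal correlation r among the test statistics.

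**1. The plan's own figure.** With 7.5 mm read as a within-subject SD, the 2×2 cross-over t-test has non-centrality 10 / (7.5 × √(2/21)) = 4.32 on 19 degrees of freedom, with critical value 2.861. Power is 91.3% at n = 21 and 89.3% at n = 20, so 21 is reproduced at alpha 0.01. Then 21 × 1.20 = 25.2, rounded up to 26. With 7.5 mm as the SD of the difference, as the text labels it, the normal formula gives (2.576 + 1.282)² × 7.5²/10² = 8.4, so 9; the paired t-test needs 12, and 21 gives 99.9% power. On either reading, 0.01 enters only as the level of the one primary test.

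**2. What 0.01 could cover.** 0.05/5 = 0.01. One primary plus four secondary domains makes five, so this may be where the figure comes from. Five independent tests at 0.01 give 1 − 0.99⁵ = 4.9%. An equal split over eleven tests would need 0.05/11 = 0.00455 each, and over twelve 0.05/12 = 0.00417.

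**3. Family-wise error for 12 tests when the methods do not differ.** For independent tests the formula is 1 − (1 − alpha)¹². For correlated tests, each statistic is written as √r times a shared normal variable plus √(1 − r) times its own, and the result is integrated over the shared part.

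| Correlation | 0.01 per test | 0.05 per test (95% intervals) |
|---|---|---|
| 0 | 11.4% | 46.0% |
| 0.3 | 10.1% | 39.7% |
| 0.5 | 8.3% | 31.9% |
| 0.7 | 6.0% | 23.2% |
| 0.9 | 3.3% | 13.5% |

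For the eleven secondary measures alone at 0.01, the figures are 10.5%, 9.4%, 7.8%, 5.7% and 3.2% in the same order. Colour, cost, adverse effects and the gender and time effects are not counted.

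**4. Reading the table.** At the level the analysis section uses, the family-wise error exceeds 5% at every correlation tried. At 0.01 it exceeds 5% for correlations up to 0.7 and is below 5% at 0.9.

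**The case against.** The strongest defence has four parts.

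First, the protocol promises no 5% family-wise error and no Bonferroni rule; it speaks only of compensating. This stands, and the 5% target is marked as an assumption throughout.

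Second, by domain the protocol has exactly five outcomes, for which 0.05/5 is right; eleven arises only if each aspect and domain is a separate test. This stands in part. It explains the choice of 0.01, but it protects only if each domain yields one test, and the text describes no single test for the specific aspects of satisfaction. It does not help with the analysis section, where five independent comparisons at 0.05 already give 1 − 0.95⁵ = 22.6%.

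Third, the measures come from the same participants, six of them from one questionnaire described as internally consistent, so correlations may be high. This also stands: at 0.9 the error at 0.01 is below 5%. A reader might infer from the count of eleven that 0.01 would leave the family uncontrolled whatever the circumstances. The document does not support that, because it gives no correlations and the answer turns on them.

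Fourth, rules for secondary outcomes often sit in an analysis plan that is not shown. For that reason the absence of a hierarchy is not the point here. The point is a stated property that the same article's analysis does not carry through.

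A reader might also infer that the primary conclusion is at risk. It is not: there is one primary outcome, and its error rate does not depend on how many secondary outcomes follow.

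**Conclusion.** The concern holds in a limited form. The article says that 0.01 compensates for the number of secondary outcomes, but its analysis reports at 95% and never uses 0.01. At that planned level the family-wise error over twelve comparisons is about 13.5% to 46%, depending on correlation. If 0.01 were applied, the figure would run from 11.4% (independent) to 3.3% (correlation 0.9), so a 5% family-wise error is not guaranteed for the secondary outcomes, although it could be met if they are very highly correlated. These sizes rest on an assumed 5% target, on counting each named aspect and domain as one comparison, and on assumed equal correlations. The test of general satisfaction and the enrolment of 26 are not affected.

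**What to change.** In the sample size section, remove the statement that 0.01 compensates for the secondary outcomes. State that the intervention effect on general satisfaction alone decides the trial, at one alpha used in both the sample size and the analysis, with the matching interval level: 99% intervals for 0.01, or 95% for 0.05. Either choice is compatible with 26 enrolled. At 21 completers, on the more demanding reading of the SD, power is 91.3% at 0.01 and 98.4% at 0.05.

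Label the secondary measures and the gender and follow-up time effects exploratory, reported as estimates with intervals and without claims of significance. If confirmatory claims on secondary outcomes are wanted, list the eleven (six MDSQ aspects, four OHIP-EDENT domains, FAD) and test them by Holm's procedure at a total two-sided 0.05, only after a significant primary result at the chosen alpha.

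The cost is a few sentences in two sections, with no extra participants or data. The downside is that some individual secondary aspects can no longer be called significant.
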